## Abstract

**Background:**

In a previous RCT we established the efficacy of the psychodynamic online aftercare programme *‘GSA-Online’* (‘Health Training Stress Management at the Workplace’) for rehabilitants with work-related stress facing return to work after long-term sickness absence. The purpose of this trial is to implement it into routine care.

**Methods/design:**

The study is performed in rehabilitation clinics with patients of different medical indications (psychosomatic, orthopedic and cardiological diseases). Rehabilitants get access to the study platform during inpatient medical rehabilitation. *‘GSA-Online plus’* integrates exploratory and motivational videos on the web application to familiarize potential participants and motivate them to follow through with it. In the 12-week writing intervention, patients write weekly online diary entries, answered by anonymous online therapists within 24 h. Primary outcome measures are the recommendation rate of *‘GSA-Online plus’* and participation rates of the rehabilitants. As secondary outcomes, psychological symptoms, overall satisfaction, helpfulness of the therapeutic feedback and utilization of *‘GSA-Online plus’* will be analysed exploratory along with the course of weekly ratings of well-being and work ability.

**Discussion:**

Meanwhile many clinical trials and meta-analysis prove that internet-based interventions are effective. This study will add insights on the dissemination and implementation of efficacious, evidence-based online treatments into medical practice. We expect a successful implementation of *‘GSA-Online plus’* in the clinical routine of the rehabilitation clinics. The focus of evaluation is on acceptance of the programme, both by the physicians in charge and the patients. In the future *‘GSA-Online plus’* could be implemented as a routine aftercare programme for rehabilitation inpatients with occupational stress.

**Trial registration:**

The trial was retrospectively registered on 6th January 2017 at ClinicalTrials.gov (Trial Registration number: ClinicalTrials Gov ID NCT03019718).

## Background

In Germany, inpatient medical rehabilitation has been implemented for patients with chronic mental and somatic complaints in order to restore and maintain work ability [1]. Approximately one third of the German population has reported significant work-related stress [2]. As we found previously, inpatients of psychosomatic rehabilitation clinics reported not only higher work-related stress, but also fewer coping resources when compared to the general German population [3]. Therefore, various work-related interventions have been adopted during inpatient medical rehabilitation treatment in order to deal with work-related stress [4]. In a previous clinical trial we could show that vocational training during inpatient psychosomatic rehabilitation improved return to work in the long run [5]. A recent meta-analysis of randomised trials for work-related medical rehabilitation interventions in patients with musculoskeletal disorders showed better return to work outcomes compared to usual medical rehabilitation [6].

Applying psychological and practical strategies acquired in rehabilitation into daily work remains a critical obstacle for many patients with chronic mental or physical disorders, particularly if they have already had long periods of sick leaves. Aftercare interventions have therefore been implemented in order to support return to work and participation in social life [7, 8]. However, few patients take part in outpatient treatments following inpatient rehabilitation because of incompatibility with their duties at work or within their families, or poor access to the outpatient rehabilitation facility [9, 10].

Internet-based interventions appear to be promising, as the great majority of the German population (84% in 2016) is online, and the internet is increasingly used for health- related issues [11, 12]. Under the heading of occupational e-mental health, internet-based interventions have been applied to deliver education, health risk assessment, work-place health promotion, preventive interventions, treatment, relapse prevention, and return-to-work assistance [13]. But online interventions focusing directly on workplace reintegration after inpatient rehabilitation are still missing. Furthermore, acceptance and uptake of online interventions is generally still limited [14] and dropout rates for psychological online interventions are often elevated [15, 16].

In order to promote successful vocational reintegration after inpatient medical rehabilitation we devised a transdiagnostic psychodynamic online aftercare programme for patients with chronic diseases (psychosomatic, cardiological, orthopaedic) [17]. This is one of the few examples of online interventions, based on a psychodynamic model [18–21]. As we could show recently, hassles with colleagues or superiors play a major role for work-related stress, fatigue and depression [22]. Another study, analysing expectations of patients toward case management after psychosomatic rehabilitation, found that most patients required support concerning conflicts at the workplace [23]. Therefore we chose a psychodynamic concept focusing on interpersonal conflicts at the workplace in our prior study [17]. In weekly writing tasks, participants were instructed to describe interpersonal situations at the workplace according to their wish, reactions of the other and their own reactions. Following the concept of the ‘Core Conflict Relationship Theme (CCRT)’ [24], the online therapist identified maladaptive relationship patterns and provided written feedback. In a randomised controlled trial (RCT) with a total of 664 participants (vs. an information only control group), we could show that the online intervention was reasonably accepted (78% of log-ins, 66% writing blogs).The majority of participants did not use the online intervention continuously, but rather six times (M = 6.00; SD = 4.21) during the possible 12 weeks [25]. Overall, psychodynamic online aftercare was effective to enhance subjective prognosis of future employment and improved psychological complaints (anxiety, depression, somatisation) as well as quality of life across a variety of chronic physical and psychological conditions, albeit with small effect sizes [25]. While most previous trials recruited over the internet, one of the strengths of our previous RCT was that we recruited patients from the rehabilitation clinics. As usual in RCTs, enrolment of participants was done by research staff based on screening criteria assessed by questionnaire. Recruitment also included a brief group intervention in each clinic by trained clinicians in order to familiarize participants with the programme and its rationale and to motivate them for participation.

## Methods/design

### Study design

Figure 1 gives an overview of the course of the trial.

**Fig. 1 Fig1:**
[figure not shown]
Overview of the course of the trial

The current study is a single group assignment with an anticipated sample size of *N* = 212 participants. We perform a combined cross-sectional and longitudinal assessment. Based on clinic routine documentation all patients admitted during the recruitment period are documented. All patients who obtain an aftercare recommendation of *‘GSA-Online plus’* and give written consent to take part in the study are followed longitudinally.

### Participants and recruitment

Recruitment is performed in three rehabilitation clinics specialized for psychosomatic, oncological, orthopaedic and rheumatic as well as cardiological diseases, which had not been involved in the previous trial. Physicians in charge received written information material about *‘GSA-online plus’* and were instructed about the inclusion criteria before recruitment started, however no formal screening of patients is involved. Patients are eligible if they a) are employed and return to their workplace within 4 weeks after inpatient medical rehabilitation, b) are able to write in German language, c) are between 18 and 59 years old and d) have a private internet access. The presence of comorbid mental disorders is not an exclusion criterion. A severe physical or mental disorder requiring an intensive treatment after rehabilitation precludes recommendation of online aftercare. Physicians are suggested to recommend the programme if indicated, according to their judgement (e.g. anticipated problems in vocational reintegration). This decision does not affect referrals for other aftercare programmes. In any case the physician responsible documents referrals for *‘GSA-Online plus’* or other aftercare recommendations and the agreement or refusal of the patient.

Patients also get a brief study information about *‘GSA-Online plus’* upon intake to rehabilitation by the medical director of the rehabilitation clinic. If they either report occupational stress or a subjective need for occupational treatment during inpatient medical rehabilitation, they may inform the clinical staff (e. g. physician, psychologist, social worker) to judge if participating at *‘GSA-Online plus’* is indicated. If patients are deemed suitable by the clinician and are interested in participating, they receive detailed verbal and written information about the study participation by a clinical employee. They also obtain access to the internet platform. Before registration all participants watch a video clip to obtain information about content and procedure of *‘GSA-Online plus’*. During the registration process all participants are asked to choose a nickname and a password and have to enter their email-address. The email-address is essential so that the participants will be informed by automated emails about study-related information, therapeutic tasks and questionnaires to be filled out. Subsequently, they log in with their nickname and a password. Then they may use information modules (video clips and written text) which aim at preparation and motivation of participants. After discharge they are able to participate fully in the 12-week programme.

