### Online intervention

The web application *‘GSA-Online plus‘* is based on the previous *‘GSA-Online‘*, which had required introduction into the programme by a clinician-led psychoeducational group [17]. *‘GSA Online plus‘ *was re-implemented from the ground up using modern web development technologies and responsive web design. It offers additional explanatory and motivational videos on the study web application to familiarize potential participants with the internet-based aftercare programme and motivate them to follow through with it. It is therefore self-explanatory for participants, as specifically devised video clips illustrate the rationale, the requirements for participants and the course of the aftercare programme. In order to stimulate emotional learning, patients are simulated by actors. Similar means of patient information and preparation have been tested previously by our group [26]. Web application and videos were developed in cooperation with the Knowledge Media Institute of the University of Koblenz-Landau and the Media Centre of the Johannes Gutenberg University Mainz.

The theoretical background of the internet-based aftercare programme is modelled after supportive expressive therapy (SET) by Luborsky [24]. The central part of SET is the ‘Core Conflictual Relationship Theme (CCRT)’ identifying recurrent and maladaptive patterns of relationships. The Identification of maladaptive interpersonal episodes with colleagues and supervisors helps to understand conflicts at the workplace and to develop potential solutions. As writing about significant own emotional experience improves the physical and mental health [27], participants are instructed to write about current (or past) meaningful interpersonal interactions with a focus on the workplace once a week, over a 12 weeks period.

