### Assessments

In order to compare study participants with non-participants, routine data are collected of all inpatients, who are admitted to the rehabilitation clinic during the period of recruitment (T0). These include demographic data (e. g. age, sex), diagnosis and work ability resp. level of functioning at discharge.

In further assessments, only participants of the study are included after they have given written consent. These questionnaires are given online with SoSci Survey [28] at www.soscisurvey.de and all data are assessed pseudonymous. Assessments will be conducted after discharge of inpatient rehabilitation, before the start of the online aftercare (baseline = T1), 1 week after the last writing-impulse is given (post-intervention = T14) as well as during the 12 weeks of the intervention (T2 to T13).

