### T2 to T13 assessments

In longitudinal assessments, once a week during the online aftercare (T2-T13), the participants` self-rated work ability is assessed by one item from the Work Ability Index [32] (‘Current work ability compared with the lifetime best.’) and the self-rated health status is measured by one item from the EQ-5D (“Your own health state today.”) [34], both on a Likert-Scale from 0 to 10. In addition, the evaluation of helpfulness and contentedness with the therapeutic feedback will be assessed.

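### T1 and the weekly ratings are tied to programme start, not to return to work, and no listed assessment records when patients return

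*Protocol article*

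**What the plan says.** All references are to the protocol article.

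- **Eligibility** (Participants and recruitment): patients "are employed and return to their workplace within 4 weeks after inpatient medical rehabilitation".
- **Programme access** (same section): "After discharge they are able to participate fully in the 12-week programme". No interval from discharge to the start is given.
- **T1** (Assessments): "Assessments will be conducted after discharge of inpatient rehabilitation, before the start of the online aftercare (baseline = T1").
- **T14** (Assessments): "1 week after the last writing-impulse is given (post-intervention = T14"). Secondary outcomes puts this at 12 weeks after T1.
- **Weekly ratings** (T2 to T13 assessments): "once a week during the online aftercare (T2-T13), the participants` self-rated work ability is assessed by one item from the Work Ability Index", with one item on health status and an evaluation of the feedback.
- **Routine data, T0** (Assessments): "These include demographic data (e. g. age, sex), diagnosis and work ability resp. level of functioning at discharge".
- **Writing task** (Online intervention): participants write about "current (or past) meaningful interpersonal interactions with a focus on the workplace once a week".

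The T1/T14 scales are listed by name, and neither that list nor the weekly list includes return status or a return date. Statistical analysis names repeated measures ANOVA and regression for prognosis of employment and depression, with no term for return to work. Objective expects regular users to do better than non-regular users and drop-outs on prognosis and distress. Discussion intends to model treatment gains by regular participation.

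**The concern.** Return to work is the event the programme is built around, and it can plausibly shift work ability, stress and mood by itself. When the time axis counts programme weeks and the return date is unknown, the same week can find one patient at home and another already back at work. A T1 rating of work ability or prognosis can likewise be a forecast for one patient and a report from the job for another.

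Two readings are exposed:

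1. A dip or rise in the weekly work-ability course could reflect patients going back to work rather than progress through the programme.
2. In the comparison by level of use, return timing could act as a confounder. It may affect use, through time to write and fresh workplace material, and it may affect prognosis and distress. The article gives no data on the link with use, so this is a possibility and not a demonstrated bias. With no control group, however, this internal comparison is the study's main evidence on gains.

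**Working it through.** The plan has no figure of its own to reproduce here. N = 212 is a recruitment forecast without alpha, power or effect size, and the point does not depend on it. What applies is timeline arithmetic.

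**Inputs**
- Return date r: 0 to 4 weeks after rehabilitation (Participants and recruitment).
- Programme length: 12 weeks (same section).
- T14: about 12 weeks after the start (Assessments, Secondary outcomes).
- Programme start s, in weeks after discharge: not stated, so varied over 0, 1, 2 and 4.
- Distribution of r: not stated. Uniform over 0 to 4 weeks is assumed for illustration only.

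**Formulas**, for s from 0 to 4
- Most programme weeks before return = 4 − s; as a share, (4 − s)/12.
- Share of patients returning after the start = (4 − s)/4 (uniform r).
- Mean programme weeks before return = (4 − s)²/8 (uniform r).

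| Start s | Most weeks before return | Share returning after start | Mean weeks before return |
|---|---|---|---|
| 0 | 4 (4/12 = 33%) | 4/4 = 100% | 16/8 = 2.0 (17% of 12) |
| 1 | 3 (3/12 = 25%) | 3/4 = 75% | 9/8 = 1.1 (9%) |
| 2 | 2 (2/12 = 17%) | 2/4 = 50% | 4/8 = 0.5 (4%) |
| 4 | 0 | 0% | 0 |

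With s = 0 and uniform r, the shares not yet back at the end of programme weeks 1, 2, 3 and 4 are 75%, 50%, 25% and 0%. The early part of the weekly course would then be an average over a changing mix of patients at home and at work.

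**T1 to T14.** A patient who meets the criterion is back by week 4 after discharge, and T14 falls at about week 12 + s. Everyone eligible is therefore back before T14. The T1 to T14 change contains the return for those whose T1 precedes it, and does not for the others.

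**Time back at work at T14** = 12 + s − r. For s and r each between 0 and 4 weeks, this runs from 12 + 0 − 4 = 8 to 12 + 4 − 0 = 16 weeks.

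**The case against.** **The start is not fixed at discharge.** A reader might infer that the 12 weeks run from discharge and that mixing is certain. The article says only that full participation is possible after discharge. Patients who start once back at work have no programme weeks before return. This stands, and the result is a range that includes zero. The unfixed start also means that the order of T1 and return is uncontrolled.

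**A return date may be collected.** This is a condensed article, and the T0 list is open-ended. The date could be in the full protocol, the questionnaires or clinic records, so its absence from the printed lists does not prove it is missing. This stands, and the fix is conditional on it. T0 describes data up to discharge, though, and return comes later.

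**Only exploratory results are touched.** The primary outcomes are the recommendation rate and use at least once. Discussion acknowledges the missing control group, so uncontrolled change is already open to concurrent events. This limits the weight of the point. It does not remove the case for recording a measurable event that bears on the comparison by use.

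**Spanning the return is intended.** This is fair. Past interactions may be written about, so weeks before return are usable. The point is about interpretation, not about programme timing.

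**Three stronger inferences are not supported.**
- One might combine the prior trial's mean of six uses with four weeks at home and say that two thirds of a late returner's entries precede return. That needs early consecutive use, and Background reports use that was mostly not continuous and gives no timing.
- One might treat the unchecked 4-week criterion as a flaw in eligibility. At referral it can only be a forecast, made without formal screening, and later non-return changes neither primary outcome.
- One might adjust for time to return throughout. Return after the start is a post-baseline event that the programme may influence, so adjustment could remove part of the association of interest or add bias.

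**Conclusion.** The point holds as a possibility of limited size. T1 and T2 to T13 are anchored to programme start, return may come up to 4 weeks after rehabilitation, and the printed assessments do not record it. Between 0 and 4 of the 12 programme weeks can precede return. The upper end requires a start at discharge and the latest permitted return, and the averages in the table rest on the assumed uniform return date.

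The weekly work-ability course, the T1 to T14 change and the comparison by level of use can each mix programme time with the return. Whether and how far they do cannot be determined from the article. This is a cheap improvement to exploratory analyses, not an error in the primary evaluation.

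**What to change.** If return status and date are already collected, say so and state how they will be used. Otherwise:

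1. Add one item to T1, the weekly questionnaire and T14 asking whether the participant is back at work and, if so, since what date.
2. Show the weekly work-ability and health course by weeks since return as well as by programme week.
3. Use at-work status at T1 as a baseline covariate in the regression of employment prognosis and depression on utilization.
4. Use time to return after programme start only descriptively or in a sensitivity analysis.
5. Report the share back at work within 4 weeks as a description, not as an eligibility check.

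The cost is one short item in existing online questionnaires, one covariate and one further display. Dates will be missing for patients who stop answering, which weakens the description most among drop-outs. At-work status at T1 does not account for differences in return timing among those who start before returning, so the comparison by use stays observational.

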### Intervention

#### Inpatient treatment

Depending on the specific chronic disease or impairment, inpatient medical rehabilitation covers diagnostic and therapeutic interventions, health education, physical training, and psychological support as indicated. At treatment termination, the responsible physician provides an assessment of work ability and of measures to improve or maintain work ability in the long run, which may include face to face aftercare interventions.

### Online intervention

The web application *‘GSA-Online plus‘* is based on the previous *‘GSA-Online‘*, which had required introduction into the programme by a clinician-led psychoeducational group [17]. *‘GSA Online plus‘ *was re-implemented from the ground up using modern web development technologies and responsive web design. It offers additional explanatory and motivational videos on the study web application to familiarize potential participants with the internet-based aftercare programme and motivate them to follow through with it. It is therefore self-explanatory for participants, as specifically devised video clips illustrate the rationale, the requirements for participants and the course of the aftercare programme. In order to stimulate emotional learning, patients are simulated by actors. Similar means of patient information and preparation have been tested previously by our group [26]. Web application and videos were developed in cooperation with the Knowledge Media Institute of the University of Koblenz-Landau and the Media Centre of the Johannes Gutenberg University Mainz.

The theoretical background of the internet-based aftercare programme is modelled after supportive expressive therapy (SET) by Luborsky [24]. The central part of SET is the ‘Core Conflictual Relationship Theme (CCRT)’ identifying recurrent and maladaptive patterns of relationships. The Identification of maladaptive interpersonal episodes with colleagues and supervisors helps to understand conflicts at the workplace and to develop potential solutions. As writing about significant own emotional experience improves the physical and mental health [27], participants are instructed to write about current (or past) meaningful interpersonal interactions with a focus on the workplace once a week, over a 12 weeks period.

Participants choose a certain day, on which they get a writing instruction (‘writing-impulse’) from their online-therapist, a trained psychologist. The writing-impulses should stimulate the participants to write their text as a diary on the web application. Participants may write one diary entry per week, and the entries are exclusively shared between the participant and the online-therapist. Participant and online-therapist communicate only via the internet-platform. Usually the participant receives an individual feedback from the online-therapist, within 24 h. All writing-impulses are personalised, depending on the last diary entry. Only the first one is standardised for all participants asking participants to describe three social encounters especially related to work. Participants are asked to note their wish in the situation, the reaction of the others and the reaction of the self. In the following weeks participant and online-therapist work out the potentially maladaptive pattern of relationship. The online-therapist also provides encouragement and support. At all times the participants and online-therapists have the opportunity to consult all instructions and diary entries. After the end of the online- aftercare participants may save the conversation as a PDF file (‘Take-home therapy-book’). The three online-therapists are psychologists/ psychotherapists in training, respectively certified in psychodynamic therapy and obtain supervision by a senior psychotherapist experienced in SET.

